#### **A multi-population approach predicts and explains motor recovery (HP1.4)**

The novel intensive HABIT-ILE therapy will be tested in two very different patient populations, namely infants with CP and adults in the chronic phase of stroke. Both populations will be imaged on the same scanner at St-Luc. The parameters of the diffusion gradients (duration, separation, intensity, waveform, orientation) and the distribution of these gradients across multiple "shells" (multi-shell HARDI) will be identical for both populations. This implies that any measured difference in DW-MRI signals arises solely from the WM tissue, which forms microstructural barriers to the diffusion of water. In other words, DW-MRI should provide a common scale to examine two seemingly different populations. The first tests on the new MRI scanner assisted by the GE-appointed MR physicist will determine whether the imaging parameters such as matrix and voxel size will be kept constant as well. At a fixed resolution, the motor tracts of infants will contain fewer voxels than those of adults given the overall size difference. Those tests will need to strike the right balance between sufficient resolution, signal-to-noise ratio and similarity between the two studies. In theory, microstructural indices derived from the advanced models described above are *not affected* by the voxel size because they provide indices that are averages over all the axons and cells of the voxel. At large voxel sizes however, several macro-environment may coexist and ultimately affect  $\mu S$  indices. Overall, we expect variables that are predictive for infants to be predictive for adults too, and conversely.

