## GRAND CHALLENGE 4: EXPLORING MECHANISMS OF TRAINING-INDUCED FUNCTIONAL RECOVERY THROUGH WM MICROSTRUCTURE IN VERY EARLY LESIONS VS ADULT ACQUIRED LESIONS

The identical experimental settings of WP 2 and 3 make it possible to directly compare WM baseline damage and training-induced changes between hemiplegic CP infants and adult stroke patients, both at the macroscopic level using whole-brain tractography and at the microscopic level using voxel-wise, model-based microstructural features. The deep underpinning of the differential repair mechanisms based on the initial conditions and age of the patients is likely to bring neurophysiological responses to the conditions allowing WM repair or training-induced changes. Investigating the best responders depending on initial conditions should help to better tailor treatment to each patient.

### RESEARCH HYPOTHESES OF GRAND CHALLENGE 4

Grand Challenge 4 will test the following hypotheses:

1. Experience-induced remodeling of the damaged CST occurs both in CP infants and adult stroke patients undergoing HABIT-ILE, but is stronger in developing CP infants **(HP4.1)**;
2. Neuroinflammation quantified by DW-MRI biomarkers is more predominant in developing CP infants compared to chronic adult stroke patients **(HP4.2)**.  
In both adult stroke patients and CP infants,
3. response to HABIT-ILE correlates *positively* with baseline DW-MRI markers quantifying the residual integrity of the damaged CST **(HP4.3)**;
4. response to HABIT-ILE correlates *negatively* with baseline DW-MRI markers quantifying a baseline enhancement of the ipsilateral, uncrossed CST **(HP4.4)**;
5. Combining DW-MRI  $\mu S$  markers of the CST with a whole-brain index of WM  $\mu S$  integrity correlates more closely with clinical response to HABIT-ILE than using exclusively the DW-MRI markers of the CST **(HP4.5)**.

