In a breakthrough exploratory step, we will try to combine functional and imaging data of CP infants and adult stroke patients using advanced model programming. Recovery in CP infants and stroke adults will be summarized and a normalization of the imaging data will be attempted for comparison in a common template. Whole-brain mapping of the two populations onto a common space may turn out to be too arduous due to very different brain sizes and large deformities in infants with CP. In that case, DW-MRI markers can always be compared after an adequate averaging over segmented sub-regions of the WM, such as the damaged or undamaged CST or regions not directly related to motor functions. Segmentation of the WM in the adult brain has become a routine task supported by many open-source software platforms. Improvements in the segmentation of the infant brain have also been gradually added to that existing software as well.

First, we hypothesize that, compared to baseline, HABIT-ILE intensive therapy induces remodeling of the  $\mu S$  indices of the damaged CST both in CP infants and adult stroke patients, but more so in developing CP infants **(HP4.1)**. The advantage of those DW-MRI indices is that their scale does not depend on brain size, brain age and are in theory only related to the morphology of the white matter independent of the imaging voxel size. If the hypothesis is verified (larger remodeling of the  $\mu S$  indexes in CP infants than in adult stroke patients), this would confirm potentially larger neuroplastic changes in the developing brain than in the aged brain, especially when combined with intensive rehabilitation, allowing for a lifespan quantification of neuroplastic potential. If the hypothesis is not verified, this would challenge the “classic” theory of larger neuroplastic potential in the developing brain.

Second, along the same line, we hypothesize that neuroinflammation quantified by DW-MRI biomarkers such as DIAMOND’s extra-axonal restricted diffusivity is more persistent in developing CP infants than in chronic

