Fourth, we hypothesize that response to HABIT-ILE correlates *negatively* with baseline DW-MRI markers quantifying a baseline enhancement of the ipsilateral, uncrossed CST (**HP4.4**), to a larger extent in CP infants than in adult stroke patients. The same procedures as for hypothesis **HP4.3** will be applied focusing on a negative correlation with the ipsilateral, uncrossed CST, expected to be stronger in CP infants. Indeed, it is expected to play a minor role, if any, in the damaged brain of adult primates (Zaaimi et al., 2012). In contrast, following early brain damage in CP, direct uncrossed axons can be preserved between the injured hemicortex and the more affected hemibody, which can thus be controlled by both sides of the brain [73]. The ipsilateral CST can therefore convey part of or all information for controlling the paretic hemibody (Guzzetta et al., 2007b). Studying carefully the relation between ipsilateral CST and response to HABIT-ILE will help further understand the mechanisms of recovery depending on initial condition, and *in fine* help fine-tune rehabilitation content regarding the initial role of the ipsilateral hemicortex and CST.

Fifth, combining DW-MRI markers of the CST with a whole-brain index of WM  $\mu S$  integrity may better predict the clinical response to HABIT-ILE than using the CST-specific markers alone (**HP4.5**). Multiple regression models will be tested to establish correlations between the clinical response to HABIT-ILE and  $\mu S$  indices of (1) the CST, (2) the corpus callosum and (3) whole-brain indices of WM  $\mu S$  integrity. Indeed, whereas a minimal level of CST integrity is undoubtedly needed to allow meaningful recovery, it becomes clear that cognitive components also play a key role in motor function recovery, at least in adult stroke patients (Rinne et al., 2018b). Exploring WM  $\mu S$  integrity beyond the CST may thus help in refining the stratification of patients in "good responders", "poor responders" and "intermediate responders".

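### HP4.4 is one label on two claims, a negative correlation in each population and a stronger one in infants, and the procedure named for it does not test the second

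*Protocol*

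**What the plan says.** All references are to the Protocol.

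- **Research hypotheses of Grand Challenge 4 (list).** HP4.3 to HP4.5 stand under "In both adult stroke patients and CP infants". HP4.4 there is a negative correlation between response to HABIT-ILE and baseline diffusion markers of an enhanced ipsilateral, uncrossed CST. The list does not say in which population it should be stronger.
- **Same list, HP4.1.** Remodelling of the damaged CST occurs in both populations, "but is stronger in developing CP infants". The list therefore states a contrast between populations where one is meant.
- **Grand Challenge 4, paragraph on the fourth hypothesis.** HP4.4 is a negative correlation "to a larger extent in CP infants than in adult stroke patients". The HP4.3 procedures are to be applied, "focusing on a negative correlation with the ipsilateral, uncrossed CST, expected to be stronger in CP infants". The reason given is that, for the ipsilateral tract, "it is expected to play a minor role, if any, in the damaged brain of adult primates".
- **Paragraph on the third hypothesis (HP4.3).** The procedures are a search for biomarkers, a level of residual CST integrity and thresholds shared by infants and adults, with a possible split into responder groups. If no common threshold is found, this is to be read as a sign of different neuroplastic potential.
- **Status.** The joint infant and adult work is introduced with "In a breakthrough exploratory step, we will try to combine functional and imaging data".

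**The concern.** The list makes one claim within each population. The text keeps that claim and adds one about the difference between populations. These are separate estimands with separate tests, and nothing says which of them decides HP4.4. If the relation is about equally strong in both populations, the list version holds and the text version does not. If it is clear in infants and absent in adults, the reverse is true. A numbered directional hypothesis whose meaning is open in this way can be reported as supported or not depending on the version chosen after the data are seen.

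The named procedure does not close the gap. It looks for what the populations share and treats failure to find it as evidence of a difference. Failing to establish a common threshold may only reflect small samples. Likewise, a significant infant correlation beside a non-significant adult one does not show that the two differ.

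**Working it through.** The protocol gives no sample size, alpha, effect size or success rule for HP4.4, so it has no figure to reproduce. The calculation only shows how far the two versions can part.

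**Inputs**
- 48 infants (Grand Challenge 2, Methods and study design) and 48 adults (Grand Challenge 3, Clinical study design). Using all 48 counts controls who receive HABIT-ILE later, so it is an upper limit.
- 24 per population if only the initially treated arms are used.
- 34 per population as a middle case: 0.70 × 48 = 33.6. The 70% is the lower bound stated for success of repeated infant MRI (section on the project's risks). Applying it to adults is an assumption.
- Assumed: r = -0.5 in infants; r = -0.5, -0.2 or 0 in adults; two-sided 0.05.

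**Assumed decision rules.** List version: a significant negative correlation in each population. Contrast: a significantly more negative correlation in infants than in adults.

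**Formulas** (Fisher z, z(r) = atanh(r), standard error 1/√(n-3))
- One population: P = Φ(|z(r)|·√(n-3) - 1.96)
- Both populations: product of the two probabilities
- Contrast: P = Φ([z(adult) - z(infant)]/√(2/(n-3)) - 1.96)

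**At n = 48** (√45 = 6.708; √(2/45) = 0.2108; atanh 0.5 = 0.5493; atanh 0.2 = 0.2027)
- Infants, -0.5: Φ(3.685 - 1.96) = 0.958
- Adults, -0.5: 0.958. Both: 0.958² ≈ 0.917. Contrast: Φ(0 - 1.96) = 0.025
- Adults, -0.2: Φ(1.360 - 1.96) = 0.274. Both: 0.263. Contrast: Φ(0.3466/0.2108 - 1.96) = Φ(-0.316) = 0.376
- Adults, 0: Φ(-1.96) = 0.025. Both: 0.024. Contrast: Φ(0.5493/0.2108 - 1.96) = Φ(0.646) = 0.741

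**Probability of support, infant r = -0.5**

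| n per population | Adult r | Each-population version | Contrast |
|---|---|---|---|
| 48 | -0.5 | 92% | 2.5% |
| 48 | -0.2 | 26% | 38% |
| 48 | 0 | 2% | 74% |
| 34 | -0.5 | 75% | 2.5% |
| 34 | -0.2 | 18% | 28% |
| 34 | 0 | 2% | 58% |
| 24 | -0.5 | 51% | 2.5% |
| 24 | -0.2 | 11% | 20% |
| 24 | 0 | 2% | 43% |

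In a simulation of the equal case (-0.5 in both, n = 48), the list version was supported and the contrast was not in about 90% of trials.

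**The case against.** **The text only refines the list.** A negative correlation present more strongly in infants naturally implies a weaker negative one in adults, the pattern that HP4.1 states openly. This stands: the two versions are compatible, and both hold if both correlations are negative and the infant one is stronger. It does not remove the gap, because the list writes the contrast out for HP4.1 and leaves it out for HP4.4.

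**The protocol does not predict a zero correlation in adults.** A reader might infer one from "it is expected to play a minor role, if any, in the damaged brain of adult primates". That phrase concerns the tract in adult primates and is offered as rationale; it is not a forecast for adult stroke patients. The 2% for the list version therefore rests on an assumed adult r of 0. At -0.2 the split is much smaller and both versions are poorly powered. The equal-correlation case shows the divergence without this phrase.

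**HP1.4 does not say the opposite.** It states that "we expect variables that are predictive for infants to be predictive for adults too, and conversely". A reader might take this as a contradiction, but it is an overall expectation about being predictive at all, and a weaker adult relation fits it.

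**The choice of test may belong in an SAP that is not shown.** This is fair as to the exact model, and the absence of an interaction term is not the point. The protocol does, however, define the hypothesis in two ways and names a procedure that cannot assess the added contrast. The HP4.3 text does foresee a difference between populations, but only by inference from failing to find a common threshold.

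**The stakes are low.** This also stands. HP4.4 is not a primary outcome, drives no sample size, and belongs to work introduced as exploratory.

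**Conclusion.** The point holds in a limited form. HP4.4 has one label and two compatible but distinct meanings, and the procedure assigned to it does not test the contrast that the text adds. The verdicts can part widely: about 92% against 2.5% under equal correlations of -0.5 and 48 per population, and about 2% against 74% if the adult correlation is 0. They part much less, 26% against 38%, if it is -0.2. These figures rest on assumed correlations, an assumed significance rule, and 48 usable participants per population. Smaller numbers lower the power of both versions.

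A reader might go further and conclude that the protocol contradicts itself or expects the list version to fail. The documents do not support that. The consequence is confined to the interpretation of a non-primary, exploratory hypothesis, but the repair is cheap and worth making before the data are analysed.

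**What to change.** 1. Word HP4.4 identically in the hypothesis list and in the paragraph on the fourth hypothesis: a negative correlation in each population, expected to be stronger in infants. Adults stay in the hypothesis. State which result counts as support for each part.
2. Report each population's correlation or slope with its confidence interval.
3. Test the contrast directly, either by comparing the two correlations with Fisher z or by a marker-by-population interaction in one regression. For the regression, standardise response within population, because the primary clinical outcome is the mini-AHA in infants and the ad-AHA in adults.
4. Do not read a failure to find a common threshold, or significance in one population only, as evidence of a difference.
5. Label the contrast exploratory and state its power. Under r = -0.5 against 0 it is 74% at 48 per population, 58% at 34 and 43% at 24; with an adult r of -0.2 it is 38%, 28% and 20%.

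HP1.4 needs no change. The cost is rewording and one added comparison, with modest power openly stated.

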## MICROMOTO: A HIGH RISK/HIGH GAIN PROJECT

The main risks are identified as

- 1) Damaged infant brains that present huge deformities might not be possibly aligned to systematic anatomical landmarks and atlases. For instance, programs as advanced as FreeSurfer still sometimes

fail to provide a reliable segmentation of the white and grey matter in brains due to the large deformities induced by the lesion. This may make it difficult to automate the detection of specific parts of the cortex (e.g., pre-motor, motor) and to cluster white matter streamlines into anatomically-identified tracts such as the cortico-spinal tract.

- 2) Most of the microstructural models in the literature, thus including those proposed in this project, have been validated for biophysical specificity (i.e., whether they non-invasively reveal what an invasive microscope analysis would show) in *animal* models using DW-MRI data acquired on preclinical scanners. The mathematical models have been applied to human data too but validation in those cases has been more empirical and generally less rigorous, due to the difficulty of performing histological studies. The main difference between preclinical and clinical MRI scanners, from a microstructure point of view, is the maximal strength of the diffusion gradients. The lower gradient intensities achievable with clinical scanners are known to impair our ability to measure the diameters of axons [Dyrby]. This is known as a resolution limit [Nilsson], whereby all diameters below about 3 microns (making up most of the brain axons) “look identical”, i.e., their signal contributions are the same and they cannot be distinguished.
- 3) Images acquisition in infants without sedation remains *per se* a huge challenge (no anesthesia in this project due to the risks associated with multiple anesthesia for young brains). Worldwide only a few teams have been able to develop processes allowing to acquire high-quality data from infants in spontaneous sleep. Although [name]’s team has recently developed a procedure and managed to acquire MRI data in 15 young children and infants, this is a major challenge in the study, especially regarding the time needed to acquire high-quality data, required for *Microstructure Fingerprinting*.
- 4) The HABIT-ILE intervention *per se* will require the participation and motivation of participants for many hours per day. This represents a potential high risk of either not meeting the high-intensity goals set in the HABIT-ILE therapy (e.g. due to lack of motivation leading to a small amount of repetitions) or of complete drop-out, both in infants and in adults who will mainly be up to 70 years of age.

Circumventing those limitations may be done via the following:

- 1) While cortical segmentation and white matter streamlines clustering should proceed fairly seamlessly in adult stroke patients, those tasks may prove more arduous in infant brains. In the worst case, segmentation will need to be performed manually based on anatomical landmarks for all 48 subjects of the CP study. However, the most likely scenario is a semi-automated framework where seeds would need to be manually placed at sites visually located on the MR images and automatic tractography would then be able to reconstruct tracts. In that way, tracts descending from specific cortical areas or the cortico-spinal tracts should be possible to reconstruct. Considering baseline biomarkers computed as average over the whole brain or over entire WM tracts is also a way to bypass the difficulty of bringing infant and adult brain into a common anatomical space.
- 2) The so-called resolution limit for axon diameters is a fundamental limitation of present-day DW-MRI technology, irrespective of the mathematical model used. However, the new GE scanner installed at Saint-Luc will deliver gradients up to 80 mT/m, the highest for any clinical system and a major improvement from the previous generation of MRI scanners, typically limited to 40-60 MT/m. Studies of sensitivity to microstructural features based on hardware constraints have been performed before and will be repeated during the preparation of DW-MRI sequences for this study, in collaboration with [name] and the MRI physicist appointed by the MRI manufacturer [SPIE16]. Those studies will clearly delineate the uncertainty on our estimates of axon diameters. Of note is that our Microstructure Fingerprinting approach was based on the most accurate modeling approach available and was specifically designed to enhance sensitivity to axon diameter. Other microstructural features of importance such as axonal orientation and axonal density, expected to play a crucial role in the reorganization of the CST during neurorehabilitation, are much less affected by gradient strength and do not suffer from the transition to clinical settings. Finally, predictive biomarkers of motor recovery

can be found even if a bias persists between the biological groundtruth and the DW-MRI –based  $\mu S$  estimates.

3) We will perform night MRIs with less noisy machines, shorter scanning sequences (possible thanks to a new equipment in our University Hospital Saint-Luc, Woluwe), very careful routines for gradual adaptation, specific installation and material for the infants. Repetitive MRIs under such conditions are successful in at least 70% of the infants[109].

4) We will provide time for participant before training to meet the team and discover the environment. Special attention will be paid in adults to the accessibility of the treatment room and the moment of the year the training will be performed (avoiding risks of contamination between fragile patients). Special attention will be paid for infants to the bonding with one therapist and providing routines during the day. Highly stimulating toys presented at the limit of reaching in the direction of movement expected and positive reinforcement will be used. These ingredients were successful in our pilot study including 4 children aged 12 to 18 months.

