## EVALUATION CRITERIA

**Primary imaging outcomes** (CST integrity measured with DTI, microstructures and myelination maps) will be measured at T0, T0+15 days and T0+90 days. We will use the classical DTI indicators of fractional anisotropy (index of fiber coherence and integrity), radial diffusivity (index of axon diameter and myelination), axial diffusivity, and mean diffusivity. These measures have been successfully used to demonstrate structural modifications of the CST, and provide an estimation of the fiber quality (Krägeloh-Mann & Cans, 2009). In addition we will use new advanced mathematical models which provide the opportunity to separately characterize fascicles of axons in areas of the brain where multiple white matter tracts intersect, allowing thus to better identify fibers of the CST from other crossing tracts, quantify CST projections, localize brain inflammation and detect axonal loss (Scheck et al., 2015). Tractography will be used to highlight potential macroscopic changes in CST organization (Bleyenheuft, Dricot, et al., 2015). Myelin maps will be used to assess global changes in myelination (Ganzetti et al., 2014). In addition, morphometric analysis (cortical thickness, cortical folding and sulcal depth) based on conventional T1 imaging will be used to investigate potential changes in grey matter (Remer et al., 2017). Resting state fMRI will also be used to explore the potential changes in brain’s functional organization and connectivity (Wen et al., 2019). All MRI data will be analyzed by an MRI specialist unaware of the treatment allocation. Although some of these measures have already been performed in infants, notably in premature babies (Deoni et al., 2015; Eaton-Rosen et al., 2017; Remer et al., 2017; Wen et al., 2019), they have never documented potential neuroplastic changes before and after an intensive intervention.

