## STATISTICAL ANALYSIS

No DTI pre-post intervention analyses in infants have been published so far. However, since CST integrity measured with DTI is highly correlated with manual ability (Bleyenheuft et al., 2007), we performed a sample size calculation based on the AHA score of the pilot study performed in 10 infants with unilateral CP (see “pilot data”). A mean improvement of 8,2 AHA units (standard deviation=5.9 AHA units) after the intensive therapy was reported. Thus, our hypothesis is an incremental improvement of 1 SD between the HABIT-ILE group and the control group (between group difference =7,2, SD=5,9). With  $\alpha=0.05$  and a  $1-\beta=0.9$ , a sample size of **15 participants per group is required**. Considering potential drop-outs and data loss in MRI, **24 participants will be included in each group**. Neuroplastic changes and secondary outcomes will be compared between groups using analysis of variance (ANOVA). Non-parametric methods will be performed whenever ANOVA assumptions are not met. Time-onset influence will be tested at the 4th assessment using an ANOVA.

Separate generalized linear models (GLM) will be estimated for the CST and whole-brain WM (ICTEAM models) to infer the correlations between  $\mu S$  integrity at baseline/after intervention and the MskL outcomes (bimanual SAT). Finally, an overall GLM will be estimated to combine CST and whole-brain  $\mu S$  integrity. The *R* software will also be used for bimanual MskL curves modelling.

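### Infant imaging outcomes are tied to a plain ANOVA over pairs of visits; one longitudinal model with a common baseline would give more precise estimates from the same scans

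*Protocol*

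**What the plan says.** All references are to the protocol; the first four items come from Grand Challenge 2 (the infant trial).

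- **Schedule.** Under Evaluation criteria, the primary imaging outcomes "will be measured at T0, T0+15 days and T0+90 days".
- **Contrasts.** Methods and Study design sets the between-group comparisons over two intervals, T0 to T+15 and T0 to T+90.
- **Method.** Under Statistical analysis, "Neuroplastic changes and secondary outcomes will be compared between groups using analysis of variance (ANOVA"), with non-parametric methods if the ANOVA assumptions fail. No baseline covariate is named.
- **Sample size.** The calculation uses mini-AHA pilot data ("between group difference =7,2, SD=5,9") and concludes that "15 participants per group is required". Then, "Considering potential drop-outs and data loss in MRI", "24 participants will be included in each group".
- **Expected scan success.** The section on the high-risk/high-gain nature of the project calls imaging unsedated infants a major challenge and says: "Repetitive MRIs under such conditions are successful in at least 70% of the infants".
- **Sister trial.** Grand Challenge 3 (stroke) describes its core design as identical to the infant trial, but its Statistical analysis section compares the same kinds of outcome by ANCOVA, adjusting for baseline.

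**The concern.** Scan loss is likely to be worst in the infant trial, yet its named method makes the least use of the scans obtained. The words ANOVA of change do not appear. They are, however, the natural reading of neuroplastic changes compared by ANOVA over two stated pairs of visits. On that reading an infant enters a contrast only when both of its scans exist. A usable scan from the third visit, or a lone scan from one of the two, contributes nothing to that contrast. Separately, a raw change score gives the baseline a fixed weight of one, which is less efficient than adjusting for it whenever the visit correlation is below one.

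At stake is the precision of the primary imaging estimates in a trial of 24 infants per arm, where each scan is hard to obtain. The estimates also rest on scan failure being unrelated to the outcome.

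**Working it through.** **1. The plan's sample size.** Normal approximation, two-sided alpha 0.05, power 0.90:

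n = 2 × (1.960 + 1.282)² × (5.9/7.2)² = 14.1, rounded up to 15 per group. This matches the plan (the t-based version gives 16). The allowance for loss is 1 − 15/24 = 37.5%.

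**2. Does 24 absorb a 30% MRI loss?** 24 × 0.7 = 16.8 per arm, above 15. Conversely 15/0.7 = 21.4, so 22, below 24. The t-test power at 7.2/5.9 = 1.22 SD with 16.8 per arm is 0.93, so the 90% target survives. The loss widens the SE by √(24/16.8) = 1.20 relative to 24 complete infants per arm.

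**3. Precision of the T0 to T0+15 contrast.** Assumptions that are not in the protocol:
- unit SD at each visit and correlation ρ between visits of 0.5, 0.7 or 0.8, equal across visit pairs;
- 70% of infants with complete series;
- data missing at random;
- covariance treated as known, so the model's gain is slightly optimistic.

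With n infants per arm having both scans:
- change ANOVA: variance = 4(1 − ρ)/n;
- ANCOVA: variance = 2(1 − ρ²)/n;
- ratio of SEs, ANCOVA to change = √((1 + ρ)/2).

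For the longitudinal model (common baseline mean, arm-by-visit effects), the variance is the generalised least squares variance of the arm difference at T0+15, summing information over every observed scan pattern.

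*Case A: the other 30% have no scans.* n = 16.8, and the model gives the same SE as ANCOVA.

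| ρ | Change ANOVA | ANCOVA = model | Reduction |
|---|---|---|---|
| 0.5 | 0.345 | 0.299 | 13.4% |
| 0.7 | 0.267 | 0.246 | 7.8% |
| 0.8 | 0.218 | 0.207 | 5.1% |

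*Case B: the other 30% have one or two scans*, spread evenly over the six possible partial patterns (5% each). One of the six contains both T0 and T0+15, so n = 24 × 0.75 = 18.

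| ρ | Change ANOVA | ANCOVA | Model | Model vs change | Model vs ANCOVA |
|---|---|---|---|---|---|
| 0.5 | 0.333 | 0.289 | 0.273 | 18.0% | 5.3% |
| 0.7 | 0.258 | 0.238 | 0.228 | 11.7% | 4.2% |
| 0.8 | 0.211 | 0.200 | 0.193 | 8.5% | 3.5% |

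(Percentages are from unrounded SEs.) In both cases baseline adjustment supplies most of the gain. Using the partial series adds about 4% to 5% beyond ANCOVA, and nothing if the affected infants have no scans.

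**The case against.** **The loss was anticipated.** This stands. The increase from 15 to 24 names MRI data loss as a reason and covers 30%. The protocol also plans night scans, shorter sequences and gradual habituation, and 70% is stated as a floor. A reader might infer that the imaging comparison is underpowered; the plan's own figures do not show that. Two limits remain. The power basis is mini-AHA, so power for the imaging measures themselves is not established. And the text also describes the effect as 1 SD, which is not 7.2/5.9; at 1 SD, 16.8 per arm would give power of about 0.80. That inconsistency is a separate matter.

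**Handling of missing data belongs in the SAP.** This also stands. The SAP is not shown, and the lack of a stated rule for failed scans is no finding. The point here is the method that the protocol does name.

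**Stronger readings of the 70%.** A reader might take it as a rate per scan, which would leave far fewer infants with both scans. The sentence counts infants with successful repeated scanning, so that does not follow. A reader might also count complete pairs, since allocation is within matched pairs. The plan sizes and compares independent groups and states no paired analysis, so pair loss does not reduce its sample.

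**Partial series are not simply dropped.** Correct. An infant with T0 and T+90 still enters the second contrast, and one with T0 and T+15 enters the first. The loss is per contrast. The protocol also does not say whether unsuccessful infants would have some scans or none, which is why both cases are shown.

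**The gain is modest.** Fair for the partial series alone. But the change costs nothing in patients or scans, and the sister trial already adjusts for baseline.

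**Conclusion.** The concern holds as a matter of precision. The infant trial fixes a plain ANOVA over two pairs of visits for an outcome measured at three, while expecting up to 30% of infants to lack a successful series. One longitudinal model would reduce the SE of the T0+15 effect by about 8% to 18% if those infants have partial series, and by about 5% to 13% if they have none. These figures depend on assumed visit correlations of 0.5 to 0.8, the assumed spread of partial patterns, a known covariance and data missing at random. They also depend on reading the ANOVA as one of change, which the text supports but does not say outright.

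The documents do not support a claim that the planned enrolment fails to cover the expected MRI loss. Nor would the longitudinal model remove bias if scan failure depends on unobserved imaging outcomes.

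**What to change.** In the Statistical analysis section of Grand Challenge 2, replace the ANOVA for imaging outcomes with one likelihood-based repeated-measures model. It should use all available scans at T0, T0+15 and T0+90, with a common baseline mean for the two arms and arm-by-visit effects. The T0+15 and T0+90 group differences are then read from this one model, and every infant with at least one usable scan can contribute. Report scan success by arm and visit, so that readers can judge whether failure looks selective.

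The cost is a change of wording: no extra infants, scans or visits. The authors must specify a covariance structure and state the missing-at-random assumption.
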